#### Professionals

Similarly it was chosen to conduct interviews with 30 professionals, meeting the inclusion criteria, and making it possible to cover the heterogeneity in terms of profession and seniority. This will make it

possible to conduct the interviews correctly in the allotted time and to have a representation within the cohort of professional heterogeneity and experience.

## 9.2 STATISTICAL METHODS USED

### 9.2.1 ANALYSIS STRATEGY

The data will be analyzed by the SHS research team to ensure cross-analysis of qualitative and quantitative data.

The main analysis will be carried out by sub-treatment for patients, i.e. the data of all participants must be analyzed with regard to the 3D printed model actually administered, even if randomization has decided otherwise, on available data.

The diagram below presents the different phases of the mixed method research proposed here. Many collection tools are used in this study to be able to study the effects of using a personalized 3D printed kidney model versus a generic 3D printed kidney model as a mediation tool on the patient experience and their interactions with professionals. This triangulation approach (21) requires specific analyses of the data obtained from the different collection tools, associated with cross-interpretations to meet the different objectives.

A descriptive analysis will be performed globally and by 3D model group.

A comparison analysis between the randomization groups will be performed, systematically without adjustment and with adjustment on the initial prognostic factors whose distribution could be, despite randomization, unbalanced.

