| 
STATISTICAL ANALYSIS OF DATA
 | 
Patients' socio-demographic and clinical data will be described in terms of frequencies for qualitative data and means and standard deviations for quantitative data, enabling comparisons to be made between the two groups of patients.
 
Data from questionnaires completed by patients will be analysed descriptively (distribution of scores obtained by patients for the HLS-EU16 literacy questionnaire at the beginning and at the end, description of the satisfaction questionnaire at the last stage). This
 
A descriptive analysis will be carried out overall and by randomisation group.
 
A comparative analysis between the randomisation groups will be carried out, systematically without adjustment and with adjustment for the initial prognostic factors whose distribution could be unbalanced despite randomisation.
 
The patient experience will be described on the basis of a cross-sectional analysis of the content of the interviews at each stage, as well as a longitudinal analysis. Changes in understanding of the disease and surgery will be studied by analysing the content of the interviews and questionnaires, and a comparison will be made between the two groups.
 
The professionals' interviews will also be analysed for content. All the analyses will be carried out with the support of Nvivo software and will be performed by the SHS researchers.
 
The data will be analysed by the team of SHS researchers to ensure cross-analysis of the qualitative and quantitative data.
 
The main analysis will be carried out by sub-treatment for the patients, i.e. the data from all the participants must be analysed with regard to the 3D printed model actually administered, even if randomisation has decided otherwise, on the basis of available data.
 |

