### 4.3. RANDOMISATION METHOD

The randomization list is established by the statistician of the Methodology Center (USMR of the Bordeaux University Hospital) before the start of the research.

The numbers of the 2 strategy groups are balanced with a 1:1 ratio, without stratification factor. A document describing the randomization procedure is kept confidentially within the Methodology and Data Management Center.

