## 9. STATISTICAL APPROACH

### 9.1 STUDY SIZE

#### Patients

The study approach is mainly of an anthropological type by systemic essence, it is based on a mixed approach with observations, interviews and questionnaires. In order to be able to combine, within the framework of the collection and then the analysis, the qualitative and quantitative approaches it was decided to build a study with 60 patients divided into 2 randomized groups of 30 patients. Patients who will have unusable data will be excluded from the analyses and replaced with a maximum total inclusion of 68 patients.

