### 9.2.3 RISK OF THE FIRST KIND

Statistical data comparison analyses will be performed at an overall risk of error of = 5%.

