### 9.3.3 ANALYSIS OF THE MAIN OBJECTIVE

The main objective is to study the effects of using a personalized 3D printed kidney model versus a generic 3D printed kidney model as a mediation tool, throughout the pathway, on the patient experience and their interactions with professionals, before and after partial nephrectomy.

The analysis of the main objective will be carried out by relying on the cross-referencing of elements from the different collection tools and will depend on the content of the interviews as well as observations. The analysis of the verbatims will be based on observational data and data from the questionnaires. A triangulation analysis of the data will therefore be carried out globally and then by group to study the differences.

A descriptive analysis will be carried out globally and by strategy group for patients on all data from the questionnaires, socio-demographic data as well as data characterizing the tumor. The description of the socio-demographic data of each of the two groups of patients (generic 3D model group / specific 3D model group) will be carried out: by indicating the frequencies (e.g.: sex, profession, etc.), the means and standard deviations (e.g.: age, illness delay, etc.) allowing the distribution of the two groups to be compared.

A comparison analysis between the groups of 3D model types will be carried out, systematically on the data from the questionnaires and the socio-demographic data.

The data from the interview transcripts will be analyzed in order to be able to study the unique life experiences of the patients as well as the common elements between patients and the heterogeneities between groups.

Observations and interviews are collection methods that do not automatically lead to a statistical analysis of the data. The statistical analysis will only cover part of the data collected, qualitative and quantitative.

The description of the patients' experience will be carried out based on the analysis of the contents of the interviews in a transversal manner for each time but also according to a longitudinal analysis taking into consideration the 3 times (T, T3 and T6) and specifying the group to which the patient belongs.

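### Adjustment covariates are picked by imbalance between arms rather than predictive value, and neither the unadjusted nor the adjusted questionnaire comparison is named as leading

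*Protocol*

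**What the plan says.** Section 9.2.1 (Analysis strategy) has the randomised groups compared, in every case, both without adjustment and "with adjustment on the initial prognostic factors whose distribution could be, despite randomization, unbalanced". The statistical part of the research summary repeats the rule: "with adjustment for the initial prognostic factors whose distribution could be unbalanced despite randomisation". Section 9.3.3 adds a comparison between model groups, carried out "systematically on the data from the questionnaires and the socio-demographic data".

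The rest of the plan bears on this as follows.

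- Section 4.3 fixes no covariate by design: "The numbers of the 2 strategy groups are balanced with a 1:1 ratio, without stratification factor".
- Section 9.3.4 spells out one between-group test of a score. The T6 minus T1 change in the literacy score is compared by a Student test, with no covariate.
- Section 9.2.5 lists only unadjusted between-group tests.
- Section 9.2.3 sets an overall error risk of 5%.
- Literacy and knowledge are both measured at T1 (section 7.4.1). Patients learn their group only at T2 (section 7.3.3).
- Satisfaction is collected once, at T6 (section 7.5).

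**The concern.** The protocol does more here than leave a detail to a later plan. It sets the criterion for choosing covariates, and an analysis plan that follows the protocol inherits it.

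The criterion looks at the wrong property. A baseline variable is worth adjusting for when it predicts the outcome. Whether it happens to differ between two randomised groups says little about that. The T1 score of the same questionnaire is the obvious candidate predictor of the later score, yet under this rule it enters only if it comes out unbalanced.

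The second problem is discretion. Both versions are always run and neither is ranked. The arms are open (section 4.2). The social-science researchers conduct the T1, T3 and T6 interviews (sections 7.4.1, 7.4.3 and 7.5) and also analyse the data (section 9.2.1). Which factors count as unbalanced, and which result is put forward, can therefore be decided with the arm-level data in view.

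At stake are the between-arm comparisons of understanding and health literacy, secondary objectives 4 and 5.

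**Working it through.** The protocol states no power, effect size or standard deviation, so there is no figure of its own to reproduce. Section 9.1 gives the size, "60 patients divided into 2 randomized groups of 30 patients", on mixed-methods grounds. Everything below uses 30 per arm and a two-sided 5% test. Effect sizes, correlations and imbalance thresholds are assumptions.

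**1. Change score against ANCOVA for literacy.** Assume a T6 effect of 0.7 SD, equal variances at T1 and T6, and correlation r between them.

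- Change score: SD of the change = √(2(1−r)), so the standardised effect is 0.7/√(2(1−r)).
- ANCOVA on T1: residual SD = √(1−r²), so the standardised effect is 0.7/√(1−r²).

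| r | Change-score effect | Power | ANCOVA effect | Power | Gap (points) |
|---|---|---|---|---|---|
| 0.3 | 0.7/1.183 = 0.592 | 62% | 0.7/0.954 = 0.734 | 79% | 17 |
| 0.5 | 0.7/1.000 = 0.700 | 76% | 0.7/0.866 = 0.808 | 86% | 10 |
| 0.7 | 0.7/0.775 = 0.904 | 93% | 0.7/0.714 = 0.980 | 96% | 3 |

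The powers come from 8,000 simulated trials per row. The non-central t distribution gives the same values to within about one point.

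Adjusting the change score for T1 gives the same treatment estimate as ANCOVA on the T6 score. The gap in the table is therefore what is lost whenever T1 is left out because it looks balanced.

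**2. Adjusting for any predictor only when it is unbalanced.** Simulations used 1 or 4 covariates, an effect of 0.736 SD, and three imbalance rules: p<0.05, p<0.10, or a standardised difference above 0.2. There were 20,000 runs per scenario with no effect and 10,000 with an effect.

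| Correlation with outcome | Unadjusted power | Imbalance rule | Named in advance | Loss from the rule (points) |
|---|---|---|---|---|
| 0.3 | about 80% | 79–81% | 80–83% | 1–3 |
| 0.5 | about 80% | 80–85% | 87–89% | 4–9 |
| 0.7 | about 80% | 82–91% | 97% | 7–15 |

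**3. Type I error in the same scenarios.**

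- Covariates named in advance: 4.8–5.4%, nominal within simulation error.
- Covariates selected by imbalance: 2.4–4.8%, so conservative.
- Either the unadjusted or the selected result counted as positive: 4.8–6.5%. The highest values (5.9–6.5%) come from the loosest rule, a standardised difference above 0.2.

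**4. How often chance flags a factor.** With 4 independent factors:

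- p<0.05: 1 − 0.95⁴ = 18.5%.
- p<0.10: 1 − 0.90⁴ = 34.4%.
- Standardised difference above 0.2: about 44% per factor, so 1 − 0.56⁴ ≈ 90%.

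The result therefore depends heavily on a threshold that the protocol does not state.

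**The case against.** Several points on the other side stand.

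- **No confirmatory test is involved.** The main criterion is a qualitative description of patient experience (section 3.1), and the sample size was not set by power. The loss falls only on supporting comparisons.
- **The unadjusted comparison is always run and is valid alone.** Every between-group test the protocol names is unadjusted, so one could say that version leads by implication. Section 9.2.1 nevertheless places the two side by side without ranking them.
- **The literacy test already uses the T1 score through the change.** At r = 0.7 only about 3 points of power are left to gain. The loss in step 1 comes from the change score itself; the imbalance rule merely fails to repair it.
- **The rule is limited to prognostic factors.** It would be unfair to model it as admitting many variables unrelated to the outcome.
- **The wording could mean factors at risk of imbalance.** With none named, observed imbalance is the natural reading, and the ambiguity itself needs removing.

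A reader might infer that baseline significance tests are the stated screen for covariates. Section 9.3.3 does compare socio-demographic data between groups, but the protocol nowhere links that comparison to the choice of covariates. A reader might also say that any imbalance must be chance. That holds for the groups as randomised. It is weaker here, because the main analysis follows the model actually received (section 9.2.1), and patients with unusable data are excluded and "replaced with a maximum total inclusion of 68 patients" (section 9.1). Neither feature makes imbalance a good criterion for adjustment.

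**Conclusion.** The point holds as a matter of efficiency and pre-specification in the secondary questionnaire comparisons. The protocol selects covariates by a property that does not measure their value, and it leaves two results without saying which leads.

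The size depends on assumptions. For literacy, ANCOVA on T1 gains about 17, 10 and 3 points of power over the planned change-score test at correlations of 0.3, 0.5 and 0.7, given a 0.7 SD effect and equal variances. For a predictor used only when unbalanced, the loss against naming it in advance is small at a correlation of 0.3 (1–3 points) and larger at 0.7 (7–15 points). The documents give no correlation from which to choose between these.

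Two stronger readings are not supported. One is that the rule makes the test unreliable. The imbalance-selected test errs on the conservative side, and inflation arises only from picking between the two results, up to about 6.5% under assumed rules. The other is a general power loss of 10 to 20 points. Losses of that size need particular assumed inputs, and the upper end needs an unadjusted follow-up score as comparator, which is not the literacy test in section 9.3.4. The main qualitative finding is untouched. The wording should be changed, but the trial does not stand or fall on it.

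**What to change.** In the research summary and sections 9.2.1 and 9.3.4, replace the imbalance rule with wording such as: *The T6 literacy score and the T3 and T6 knowledge scores are compared between arms by ANCOVA adjusted for the T1 score of the same questionnaire, whatever the observed balance. This is the main quantitative result, and the unadjusted comparison is supportive. Any further covariates are fixed before any arm-level comparison and are not chosen by imbalance. Satisfaction, measured only at T6, is compared without a baseline score.*

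In section 9.3.3, describe baseline characteristics by arm and state that tests on them are not used to choose covariates.

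No new data are needed, since section 7.4.1 already collects both T1 questionnaires. The cost is consistent rewording in four places, a covariate list that must be fixed in advance, and a regression model in place of a t-test.

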### 9.2.2 PATIENTS INCLUDED IN THE ANALYSIS

Only patients and professionals who present at least one of the following conditions may be excluded from the analysis:

- Patients wrongly included due to unsigned consent;
- Patients or professionals wrongly included due to major eligibility criterion(s) not met;
- Patients or professionals who have withdrawn their consent.

This exclusion decision will be taken by the Scientific Council without the knowledge of the randomization group and the patient's progress after inclusion.

Apart from these exclusions, patients or professionals who have died, been lost to follow-up or have abandoned the research will all be included in the analysis.

### 9.2.3 RISK OF THE FIRST KIND

Statistical data comparison analyses will be performed at an overall risk of error of = 5%.

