3D models will be presented to the patients according to the allocated study group during a preoperative education consultation. All patients will complete questionnaires about their health literacy level, their knowledge of kidney anatomy and tumor and their satisfaction about the using 3D-printed kidney models as educational mediation tools. Semi-structured interviews will be conducted at three different times: between the first consultation with the surgeon and the preoperative education consultation, between this second consultation and the surgery and after the post-operative consultation.

Primary outcome:

To study the effects of using a personalized versus a generic 3D-printed kidney model as a mediation tool on patients' experience and interactions with carers, before and after partial nephrectomy.

This is a mixed-type study designed to combine data from different collection tools (observations, interviews and questionnaires). The criteria studied are:

For the patient:

- Qualitative assessment of the patient experience
- Changes in the average score of the HLSEU-Q16 literacy questionnaire - Level of understanding of renal anatomy and of the surgical issues

For the carers:

- Qualitative assessment of changes in practice following the integration of 3D models into the department

Secondary outcomes:

1. Description of interactions between carers and patients, specifying the situations and the environments, the practice, vocabulary and content of the discourse used during the entire care process.
2. Comparison of the differences in speech and terminology used when using the different tools during interactions between patients, carers and patients' entourage with systematic analysis of interviews.
3. Studying the use of the 3D-printed kidney model introduced during the medical information consultation up to the post-operative visit by describing the life of the model throughout the entire care process (from the inclusion visit to the post-op visit).
4. Comparison of the patient's understanding of anatomy and surgical strategy according to the type of tool (personalized vs generic 3D printed model) before and after the surgery (T1, T3 and T6).
5. Comparison of the level of health literacy between the two groups at different times with changes in the average score on the literacy questionnaire (HLSEU-Q16: European Health Literacy Survey Questionnaire; T1 and T6).

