### 3. ASSESSMENT CRITERIA

#### 3.1. MAIN ASSESSMENT CRITERIA

##### Qualitative assessment of the patient experience

This is not a single criterion, but a set of elements used to describe the patient experience based on the interviews. Observations and the three questionnaires used (literacy, knowledge and satisfaction questionnaires: appendices 1, 2 and 3) complete the analyses of the qualitative data. The patient experience collected will also be analysed in relation to the clinical and demographic data from the UroCCR database.

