#### 3.2. SECONDARY ASSESSMENT CRITERIA

Course of interactions between professionals and patients: description of the course of interactions according to the model used, specifying the practice as well as the vocabulary and content of the discourse used.

Frequency of terms used in accordance with the use of the different tools during interactions: comparison of the differences in discourse and terminology when using the different tools

during interactions between patients, carers and the patient's entourage with the systematic analysis of the interviews.

Use of the 3D model during care: description of the life of the model throughout care (from the inclusion visit to the post-operative visit).

Level of understanding of renal anatomy and surgical issues measured using the translation of the questionnaire proposed by Bernhard et al (1) (appendix 2). This questionnaire consists of 4 parts: physiological and anatomical dimensions, knowledge of the disease and tumour characteristics, understanding of the surgical procedure and associated risks of complication. These dimensions will be studied before and after the presentation of the model and compared according to the model used. The final part of the questionnaire, based on the evaluation of patient satisfaction, will be presented at the end of the post-operative consultation period (T6) (Appendix 3).

Evolution of the mean score of the HLSEU-Q16 literacy questionnaire measured (health literacy)

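### Section 9.2.3 promises an overall 5% error risk that the planned tests do not deliver as written, and the abstract lists literacy and understanding as both primary and secondary

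*Protocol*

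**What the plan says.** **Error risk.** Protocol section 9.2.3 is one sentence: "Statistical data comparison analyses will be performed at an overall risk of error of = 5" per cent.

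**Planned tests.**
- Section 9.3.4 names two paired t tests of HLSEU-Q16 between T1 and T6 (one per arm), a t test of the change between arms, and a paired chi-square comparison over time of the score in three levels.
- Section 9.3.3, under the main objective, adds a comparison between model types, "systematically on the data from the questionnaires and the socio-demographic data".
- Section 9.2.1 has the group comparisons run both unadjusted and adjusted. The adjustment factors are not fixed in advance.
- None of these sections states a multiplicity correction, a testing order, one confirmatory comparison or an exploratory label.

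**Status of the outcomes.**
- Section 3.1, main criterion: "This is not a single criterion, but a set of elements used to describe the patient experience based on the interviews". This interview material is completed by observation and by the three questionnaires.
- Section 3.2 lists as secondary: "Level of understanding of renal anatomy and surgical issues measured using the translation of the questionnaire", the change in HLSEU-Q16 score, and the effects on professionals.
- The abstract's primary outcome block lists, for the patient, the qualitative experience and then "Changes in the average score of the HLSEU-Q16 literacy questionnaire - Level of understanding of renal anatomy and of the surgical issues". For carers it lists changes in practice.
- The abstract's secondary outcomes repeat understanding (item 4), literacy (item 5: "Comparison of the level of health literacy between the two groups at different times with changes in the average score on the literacy questionnaire") and changes perceived by carers (item 6).

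**The concern.** An overall risk of 5% normally means that the chance of any false positive across the comparisons is at most 5%. That holds for a single test, or for several tests with a procedure that shares out the error. The protocol plans several tests and states no such procedure.

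The outcome lists make this matter more. The main criterion in 3.1 carries no hypothesis test. The measures that are tested, literacy and understanding, appear under the primary heading in the abstract, and questionnaire comparisons sit under the main objective in 9.3.3. A report could take a questionnaire p<0.05, call it primary on the strength of the abstract, and cite 9.2.3 for a 5% error risk. The trial is open-label, and the same research team conducts the interviews and analyses the data, so clear prespecification is worth having.

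**Working it through.** **Inputs from the protocol.** Overall error 5% (9.2.3); 30 patients per arm (9.1); the tests named in 9.3.4; four satisfaction items (Appendix 3); understanding measured at T1, T3 and T6 (abstract).

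**Assumptions.** Two-sided tests, each at 5%; no true effect; normal data in the simulations.

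**1. The plan's own figure.** With k independent tests at 5%, the chance of at least one false positive is 1 − 0.95^k. For k = 1 this is 5%, so the stated figure is reproduced only for one test.

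**2. Named literacy tests.**
- Three t tests (two within-arm, one between-arm): 1 − 0.95³ = 14.3% if independent.
- The between-arm test uses the same change scores as the two within-arm tests. Simulating that structure (30 per arm, 200,000 runs) gives 11.3%.
- Adding one three-level test: 1 − 0.95⁴ = 18.5% if independent. That test reuses the same scores, so the real figure is lower.

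**3. Between-arm tests after the model is shown.** The protocol gives no count. Assume HLSEU-Q16 change (1), understanding total at T3 and T6 (2) and the satisfaction items (4): 1 + 2 + 4 = 7.

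| Pairwise correlation | Chance of at least one false positive |
|---|---|
| 0 | 1 − 0.95⁷ = 30.2% |
| 0.3 | 27.2% |
| 0.5 | 22.9% |
| 0.8 | 14.9% |

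The last three rows are from simulation. Adjusted re-runs of the same comparisons would add to all of these figures.

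**4. Only the two patient questionnaire measures with double status.** Literacy change and one understanding score: 1 − 0.95² = 9.8% if independent, 7.8% at correlation 0.8.

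**5. What a correction would cost.** The standardised difference detectable with 80% power is (z for two-sided alpha + 0.842) × √(2/30).
- At alpha 0.05: (1.960 + 0.842) × 0.258 = 0.72.
- At 0.05/7 = 0.0071: (2.690 + 0.842) × 0.258 = 0.91.

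**6. Outcome status side by side.**

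| Measure | Abstract, primary block | Abstract, secondary list | Section 3.1 | Section 3.2 |
|---|---|---|---|---|
| Patient experience (interviews) | yes | – | main criterion | – |
| HLSEU-Q16 change | yes | item 5 | questionnaire completes the interviews | secondary |
| Level of understanding | yes | item 4 | questionnaire completes the interviews | secondary |
| Effects on carers | yes | item 6 | – | secondary |

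The conflict lies inside the abstract itself as well as between the abstract and section 3.

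**The case against.** **A correction may be in the SAP.** No sentence in the protocol says that each test is run at 5%, and a procedure could be set elsewhere. This stands as a limit: the percentages above are conditional on 5% per test. But 9.2.3 already claims the property, the protocol's own analysis plan names tests without the means to deliver it, and an SAP would not remove the double listing in the abstract.

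**The word may be a translation slip.** The text is translated and a symbol seems to be lost before the equals sign, so a generic alpha statement may have been meant. That is possible. The sentence would then misstate the intention and still need rewording.

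**The study is mainly qualitative.** Section 9.1 gives it a chiefly anthropological approach with no power claim, and the summary and abstract describe the questionnaire data as analysed descriptively. This is a good argument for calling the tests exploratory. It does not support an overall 5% claim.

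**Stronger readings that a reader might infer:**
- *About 18 tests and a 60% risk* (1 − 0.95¹⁸ = 60.3%). That takes three literacy t tests, two three-level tests, nine understanding tests (three parts at three times) and four satisfaction items. The protocol specifies neither the part-by-time breakdown nor a three-level test per arm. Three of the nine fall at T1, before the model is shown or the allocation disclosed to the patient, and four of the 18 are within-arm changes that do not compare the models. Removing those seven leaves 11 (43% if independent); using understanding totals leaves the seven used above.
- *The main criterion is purely qualitative.* The summary calls it mixed, 3.1 gives the questionnaires a completing role, and 9.3.3 triangulates them.
- *Any questionnaire item could be claimed as primary.* The abstract's primary block does not include satisfaction, so the risk concerns literacy and understanding.
- *The registry entry is wrong.* It is not available here and cannot be judged.

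**Conclusion.** The point holds in two parts. First, the overall 5% in 9.2.3 is not delivered by the plan as written: at 5% per test, the risk is about 11% to 14% for the three named literacy t tests and about 15% to 30% for an assumed seven between-arm tests. The test count, the 5% per test and the correlations are assumptions, so only the direction is firm: any count above one, without a correction, exceeds 5% unless the tests are perfectly dependent. Second, the abstract gives literacy, understanding and effects on carers both primary and secondary status, against 3.1 and 3.2. Together these leave room to present a literacy or understanding p-value as a primary result at an error risk it does not have. The sample size of 60 is not called into question; it rests on no formula.

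**What to change.** Reword 9.2.3, for example: *Each quantitative comparison is two-sided at 5%, without multiplicity control; all are secondary and exploratory, reported as estimates with 95% CI, and no confirmatory claim is made.* The comparisons mentioned in 9.2.1 and 9.3.3 then fall under the same rule.

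Align the abstract's primary outcome block with 3.1 and 3.2. Primary: interview-based patient experience, with the questionnaires only as supporting descriptive material for triangulation. Secondary: the tests on literacy and understanding, and the assessment of effects on professionals. Check that the registered outcomes agree.

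The cost is a wording change, with no new data, patients or procedures. The sponsor gives up the claim of an overall 5% risk. Keeping that claim through a Bonferroni correction over seven tests would raise the detectable standardised difference from 0.72 to 0.91, so the exploratory label is the more proportionate choice for this study.
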